### Study design

This is a prospective, single-center, randomized, parallel-group, interventional, assessor-blinded trial conducted at the Department of Urology of the Bern University Hospital, Switzerland. We expect to randomize the first patient in August 2014.

### Blinding and randomization

Assessment of the endpoint data will be performed in a blinded manner. The study nurse responsible for data acquisition will not be allowed to see the content of the crystalloid infusion. Laboratory, defecation, flatus, and body weight data will be assessed electronically in the nurse ward office using the CGM Phoenix Workstation 7-i-PDOS^©^; it will not be assessed in front of the patient.

Randomization will be carried out using a computer-generated list with 11 blocks of 4 patients per block. Allocation will be stored in sealed opaque and numbered envelopes. Patients will be included strictly in numerical order.

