**Methods and design:**

This is an investigator-initiated, single-center, randomized, controlled, parallel group trial with assessor-blinded outcome assessment, in the Department of Urology, University Hospital Bern, Switzerland. The study will involve 44 patients with bladder cancer scheduled for radical cystectomy and urinary diversion. The primary outcome is the duration between the end of surgery and the return of the GI function (first defecation). Secondary outcomes are fluid balance (body weight difference postoperatively versus preoperatively) and the incidence of kidney function disorders according to the Risk – Injury – Failure – Loss - End Stage Renal Disease (RIFLE classification). An equal number of patients are allocated to receive Ringerfundin® solution or a glucose/potassium-based balanced crystalloid solution as baseline infusion during the entire time that intravenous administration of fluid is necessary during the perioperative period. The randomized crystalloid solution is infused at a rate of 1 ml/kg/h until the bladder has been removed, followed by 3 ml/kg/h until the end of surgery. Postoperative hydration is identical in both groups and consists of 1,500 ml of the randomized crystalloid solution per 24 hours. Postoperative patient care is identical in both groups; patients are allowed to drink clear fluids immediately after surgery, and liquid diet is started on postoperative day 1, as well as active mobilization and the use of chewing gum. Body weight is measured daily in the morning. Time of first flatus and first defecation are recorded.

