### Time course of the study and collection of the data

#### Admission day

After informed consent, patients undergoing open radical cystectomy with urinary diversion will be randomized, according to the concealed numbered envelopes. Preoperative blood samples will be taken (plasma samples: Na, K, Cl, Mg, HPO_4_, glucose, osmolality, renin, aldosterone, arginine-vasopressin, BNP; urine samples: NGAL, Na, Cl and osmolality) and body weight documented. In addition, preoperative American Society of Anesthesiologists (ASA) physical status score, Charlson comorbidity score, and Glasgow prognostic score will be recorded.

Included patients will be requested to note the time of first flatus and to inform the ward nurses accordingly. During the first 5 postoperative days, patients will stay on the intermediate care unit; this will allow rapid assessment of the first flatus and defecation as patients will be continuously monitored and will have at least one visit by the nurse per hour. Assessment of the first flatus and defecation will be electronically documented (including time of event).

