### Study intervention

An equal number of patients will be randomized to receive either Ringerfundin® solution or G5-K crystalloid solution as baseline infusion during the entire period that an intravenous administration of fluid is necessary (Table 1). The G5-K crystalloid solution is already used as a baseline infusion on our intensive care unit, and has been shown to be safe.

**Table 1 T1:** Electrolyte composition of the two different crystalloid solutions

**Electrolyte**	**Ringerfundin®**	**G5-K solution**
Sodium	145.0 mmol/l	50.0 mmol/l
Potassium	4.0 mmol/l	30.0 mmol/l
Magnesium	1.0 mmol/l	2.0 mmol/l
Calcium	2.5 mmol/l	0 mmol/l
Chloride	127.0 mmol/l	0 mmol/l
Acetate	24.0 mmol/l	0 mmol/l
Maleate	5.0 mmol/l	0 mmol/l
Lactate	0 mmol/l	18 mmol/l
HPO_4_	0 mmol/l	8.0 mmol/l
Glucose	0 mmol/l	50 g/l

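### A fixed, published block size of 4 at one centre, with infusion masking described only for the study nurse, lets anyone who tracks earlier allocations deduce one third of them on average

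*Protocol article*

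**What the plan says.** On allocation, the Blinding and randomization section states: "Randomization will be carried out using a computer-generated list with 11 blocks of 4 patients per block". It adds: "Allocation will be stored in sealed opaque and numbered envelopes", with envelopes used in strict numerical order. The abstract gives the total: "The study will involve 44 patients with bladder cancer scheduled for radical cystectomy and urinary diversion". The Study intervention section gives the ratio: "An equal number of patients will be randomized to receive either Ringerfundin® solution or G5-K crystalloid solution". No stratification and no variation in block size is described. The article is dated 8 July 2014, and the Study design section expects the first randomization in August 2014.

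On timing, the Admission day section places randomization after informed consent.

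On masking, the design is called assessor-blinded. The only restriction described on seeing the infusion is: "The study nurse responsible for data acquisition will not be allowed to see the content of the crystalloid infusion". The Registration and record-keeping section repeats that this nurse does not know the group. For the data themselves: "Laboratory, defecation, flatus, and body weight data will be assessed electronically in the nurse ward office", and not in front of the patient. The Admission day section also says: "Included patients will be requested to note the time of first flatus and to inform the ward nurses accordingly". It provides for a nurse visit at least hourly and for electronic documentation of flatus and defecation with the time of the event, but does not name who makes that entry.

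**The concern.** Sealed opaque envelopes protect the allocation that has not yet been opened. They do not prevent deduction of the next allocation from those already in use. That needs two things: knowing the block size, which is published, and knowing which solution earlier patients received. The article describes nothing that would hide the solution from anyone but the study nurse.

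Foreknowledge matters most at the moment of approach and consent, which comes before the envelope is opened. If a patient expected to recover bowel function slowly is approached or passed over depending on the arm that is due, the groups can differ at baseline in ways that the primary comparison of time to first defecation cannot correct. The sample size section plans on 18 evaluable patients per group, so a few steered patients could carry weight. The documents give no basis for expressing such a bias in days.

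A lesser matter is the scope of the assessor blinding. The study nurse reads event times from the electronic record in an office, so someone else appears to have entered them first. The same nurse also handles the laboratory data.

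**Working it through.** **Inputs.** Blocks: 11 of size 4 (Blinding and randomization). Total: 44 (abstract). Ratio: 1:1 (Study intervention), with 22 per group (Sample analysis). Caseload about 100 a year and recruitment over 18 months (Duration and timeline). *Assumption:* each block is balanced 2:2. Equal allocation implies this, but it is not written.

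**The plan's own figure.** 11 × 4 = 44 = 2 × 22, so the list agrees with the stated total.

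**Certain allocations, fixed blocks of 4.** There are six equally likely 2:2 sequences. A position is certain once one arm is used up in the block.
- AABB and BBAA: the third and fourth positions are certain (2 each).
- ABAB, ABBA, BAAB and BABA: only the fourth is certain (1 each).
- Expected number per block: (2 × 2 + 4 × 1)/6 = 8/6 = 1.333.
- Share: 1.333/4 = 8/24 = 33.3%.
- Over 11 blocks: 11 × 1.333 = 14.7 of 44. Minimum 11 × 1 = 11; maximum 11 × 2 = 22.

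**Best-guess success, fixed blocks of 4.** The guesser always names the arm used less so far in the block (the Blackwell-Hodges convergence strategy).
- Position 1: 1/2.
- Position 2: 2/3.
- Position 3: certain with probability 1/3, tied with probability 2/3, so 1/3 × 1 + 2/3 × 1/2 = 2/3.
- Position 4: 1.
- Mean: (1/2 + 2/3 + 2/3 + 1)/4 = 17/24 = 70.8%, or 31.2 of 44, against 22 by chance.

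**Alternatives.** A larger fixed block helps only partly: the same enumeration leaves 25% certain for blocks of 6 and 20% for blocks of 8. Randomly varying sizes were simulated (4,000 trials of 44 patients, last block cut at 44). The observer knows the possible sizes and sees every earlier allocation, but does not know the order of the sizes.

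| List | Certain | Of 44 | Best guess correct |
|---|---|---|---|
| Fixed 4 (exact) | 33.3% | 14.7 | 70.8% |
| Fixed 4 (simulated, as a check) | 33.2% | 14.6 | 70.9% |
| Random 4 and 6 | 5.6% | 2.5 | 69.0% |
| Random 2, 4 and 6 | 4.0% | 1.7 | 70.0% |

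**Opportunity.** 44/18 = 2.4 patients a month, so the previous patient's infusion will usually have started before the next consent. 100 × 1.5 = 150 cystectomies are expected for 44 places. Not all 150 will be eligible or willing, so the gap of 106 is an upper limit on the room for selection.

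**The case against.** The one-third figure is what a recruiter who keeps a complete tally could deduce. The article does not say who holds the list, who opens the envelopes, or whether those who recruit at the preoperative assessment learn which solution earlier patients received in theatre and on the intermediate care unit. Recruitment is to be consecutive, consent comes first, and envelopes are used in order. A nurse outside recruitment, randomization and assessment verifies consent and eligibility for all patients. These safeguards narrow the room to steer, and that part of the objection stands. They do not remove the deduction. Verification as described concerns enrolled patients and says nothing about those not approached.

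It is also fair that varying the block size hardly lowers the best-guess rate. The gain is in certainty only.

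On the outcome, a reader might infer that unmasked ward nurses record the primary endpoint. The documents do not establish this. The sentence about informing ward nurses concerns flatus, a secondary outcome. The person who enters the defecation time is not named, and masking of the bags may be described in the full protocol. First defecation is also a fairly objective event, recorded with its time under hourly visits.

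A reader might further infer that the laboratory values give away the arm and that the blinding is therefore empty. The solutions do differ in chloride (127 against 0 mmol/l) and potassium (4 against 30 mmol/l). But both groups can receive Ringerfundin as boluses and blood-loss replacement, plasma values are physiologically regulated, and nothing in the article shows that the arm can be read from them.

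**Conclusion.** The point on block size holds. With 2:2 blocks and knowledge of earlier allocations, 33.3% of allocations are certain in advance: 14.7 of 44 expected, 11 at least and 22 at most. The published, fixed size supplies half of what is needed for the deduction, and no described measure withholds the other half from recruiting staff. This is an avoidable weakness in concealment. It is not evidence that allocation has been or will be subverted, and 14.7 is the number that could be deduced, not a number known to anyone.

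On outcome assessment, the documents support only a narrow statement. The described blinding applies to the study nurse who extracts the data, while event times appear to be entered first by bedside staff whose masking is not described. That is an inference, and it calls for clarification and a simple ordering rule.

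**What to change.** Before the first patient is randomized, regenerate the list of 44 with randomly varying block sizes, for example 4 and 6 or 2, 4 and 6. Complete blocks can still total 44: five of 4 and four of 6 give 20 + 24 = 44. Someone outside recruitment should prepare the list, and the sizes should not be disclosed to recruiting staff or published before enrolment ends. The simulated 4% to 6% is approximate for a list made to total exactly 44. The change removes most of the certainty but leaves guessing near 70%, so it should not be described as making allocation unpredictable.

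As a secondary step, have the study nurse extract defecation and flatus times before opening the laboratory data. State that assessor blinding covers data extraction, and say who enters the event times and whether they know the arm.

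The cost is a new list and a new set of envelopes. The ordering rule and the added wording cost almost nothing.

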### Selection of the participants

Consecutive patients with bladder cancer will be identified and recruited during the preoperative assessment of eligibility for an open radical cystectomy with urinary diversion. Participants fulfilling the inclusion criteria will be asked for their signed informed consent as required by the local ethics committee, and in accordance with the Declaration of Helsinki.

Inclusion criteria are age ≥18 years old, type of surgery (open radical cystectomy with urinary diversion; that is, ileal conduit, orthotopic bladder substitute, catheterizable ileal pouch), American Society of Anesthesiologists (ASA) physical status II and III, and written informed consent.

Exclusion criteria are pregnancy, breast-feeding (which are exclusion criteria for this type of surgery itself), congestive heart failure (New York Heart Association (NYHA) classification ≥3), severe hepatic disease (prothrombin ratio <50%), and significant renal dysfunction (estimated glomerular filtration rate <45 ml/min).

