### Statistics

Data will be analyzed by the research team in collaboration with a medically versed biostatistician. There will be no interim analysis.

Statistical analysis will be conducted on an intention-to-treat basis. Data distribution will be tested by Q-Q plots. Normally distributed data will be presented as mean and standard deviation (SD), skewed data as median and range, and dichotome data as number and percentage. Comparing related and unrelated continuous samples, the paired and unpaired *t*-tests, respectively, will be used for normally distributed data and the Wilcoxon signed rank test and Mann–Whitney *U*-test, respectively for skewed data. Differences in proportions will be analyzed using the Fisher’s exact test, and risk ratio with associated 95% confidence interval (CI). For the analysis of the primary endpoint, we will use the unpaired Student *t*-test with associated 95% CI. In addition, a multiple logistic regression analysis will be carried out, including the randomization groups and all clinically relevant variables (age, ASA scores, Charlson comorbidity score, Glasgow prognostic score, postoperative fluid balance). A two-sided *P* value of less than 0.05 will be considered significant.

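### Three urinary diversions are eligible, but diversion type is neither balanced by the randomisation nor named for adjustment, so a chance imbalance would go uncorrected

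*Protocol article*

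**What the plan says.** All references are to the protocol article.

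- **Selection of the participants.** The surgical criterion is met by any of three operations: "type of surgery (open radical cystectomy with urinary diversion; that is, ileal conduit, orthotopic bladder substitute, catheterizable ileal pouch".
- **Blinding and randomization.** "Randomization will be carried out using a computer-generated list with 11 blocks of 4 patients per block". The envelopes form one sequence: "Patients will be included strictly in numerical order". No stratification factor is named.
- **Statistics, primary test.** A *t*-test, which is unadjusted: "For the analysis of the primary endpoint, we will use the unpaired Student".
- **Statistics, adjusted model.** "In addition, a multiple logistic regression analysis will be carried out, including the randomization groups". The other terms in this model are given as "all clinically relevant variables (age, ASA scores, Charlson comorbidity score, Glasgow prognostic score, postoperative fluid balance". The bracket has no such wording as 'for example', so it reads as a complete list. Diversion type is not in it. The model's outcome is not named.
- **Admission day.** ASA, Charlson and Glasgow prognostic scores are the baseline scores to be recorded. The planned diversion is not mentioned.
- **Background.** Cystectomy patients as a whole are described as prone to creatinine rises, electrolyte disturbance and acidosis, and at risk of constipation or ileus. Nothing is broken down by type of diversion.

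**The concern.** The primary outcome is a bowel outcome, and several secondary outcomes concern pH, chloride and other electrolytes. All three eligible operations are urinary diversions, and it is plausible that they differ in bowel recovery or acid-base behaviour, although the article does not say that they do. If they differ, an arm that happens to receive more of one operation will show a difference that can be mistaken for an effect of the fluid.

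The point goes beyond missing detail. The article fixes the allocation scheme and sets out a covariate list that presents itself as complete. That list includes postoperative fluid balance, which is measured after randomisation, but not the operation, which is a plausible prognostic factor. A later analysis plan that added diversion would depart from the published list.

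**Working it through.** **1. The list has no strata.** 11 blocks × 4 = 44 = 2 × 22. One sequence covers the whole planned sample, so balance is enforced on the number per arm only.

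**2. How likely is an imbalance?** Inputs from the article: 44 patients, 22 per arm. Assumptions: diversion is reduced to two classes (conduit versus the two continent reservoirs), and one class has *K* = 13 to 22 of the 44 patients (30–50%).

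If *x* of the *K* patients fall in one arm, *x* is hypergeometric(44, *K*, 22), and the difference in share is |2*x* − *K*|/22. A gap of at least 20 points needs |2*x* − *K*| ≥ 4.4. That means at least 5 when *K* is odd (5/22 = 22.7 points) and at least 6 when *K* is even (6/22 = 27.3 points).

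| *K* | Event | Probability |
|---|---|---|
| 13 | *x* ≤ 4 or ≥ 9 | 0.185 |
| 14 | *x* ≤ 4 or ≥ 10 | 0.104 |
| 15 | *x* ≤ 5 or ≥ 10 | 0.203 |
| 18 | *x* ≤ 6 or ≥ 12 | 0.124 |
| 21 | *x* ≤ 8 or ≥ 13 | 0.227 |
| 22 | *x* ≤ 8 or ≥ 14 | 0.131 |

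Over *K* = 13 to 22 the range is about 10–23%, both directions counted. Simulating permuted blocks of 4, with each patient's class drawn at random, gives 14–18% for 44 patients and 20–24% for 36 evaluable patients.

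**3. How far would the estimate move?** Shift = imbalance × difference in first defecation between classes (*d*). The article gives no *d*, so the range 0 to 1 day is an assumption.

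- *d* = 0: shift 0.
- *d* = 0.5 day: 0.20 × 0.5 = 0.10 to 0.27 × 0.5 = 0.14 day.
- *d* = 1 day: 0.20 to 0.27 day.

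Against the 1-day target this is 0 to 27%.

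**4. Is the top of that range plausible?** Variance between classes is *p*(1 − *p*)*d*². At *d* = 1 and *p* = 0.3 to 0.5 this is 0.21 to 0.25. The retrospective SD of 0.82 days (Sample analysis) gives a total variance of 0.82² = 0.67. If that cohort had a similar mix of operations, diversion alone would account for 0.21/0.67 = 31% to 0.25/0.67 = 37% of all variation. A 1-day class difference is therefore an upper bound rather than an expectation.

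**5. What does this do to the test, and what does adjustment do?** Simulation: 44 patients, blocks of 4, 50% in each class, total SD within arm 1 day, 20,000 trials per setting. The unadjusted *t*-test is compared with a linear model containing group and diversion class.

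| *d* (days) | Type I error, unadjusted | Power for a 1-day effect, unadjusted | Power, adjusted |
|---|---|---|---|
| 0 | 0.050 | 0.896 | 0.889 |
| 0.5 | 0.054 | 0.900 | 0.910 |
| 1 | 0.049 | 0.899 | 0.957 |

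Adjustment costs 0.896 − 0.889 = 0.7 point of power if diversion is irrelevant. It gains 1.0 point at *d* = 0.5 and 5.8 points at *d* = 1.

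In about 9% of trials the G5-K arm has at least 20 points more of the slower class. In those trials the unadjusted estimate moves by about 0.13 day (*d* = 0.5) or 0.28 day (*d* = 1), and power falls to 0.80 or 0.67. The adjusted model removes the shift (0.01 day or less) and has power 0.88 or 0.95.

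The article's sample-size figure of 18 per group plays no part in this check.

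**The case against.** The case against is substantial, and most of it limits the point rather than removing it.

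- **A reader might infer that the trial is biased.** It is not. Randomisation makes the expected imbalance zero, and the simulated type I error of the unadjusted test is about 5%. Not stratifying a single-centre trial of 44 patients is a legitimate choice, and the same argument could be made for other unstratified baseline factors.
- **The prognostic premise is not in the article.** No section compares the three operations on bowel recovery or electrolytes. If diversion has no effect there is no distortion, so the range must start at zero.
- **A reader might treat the 1-day SD as variation within a diversion class and add a diversion component to it.** The article does not support this. It is the SD assumed for the comparison of groups and already exceeds the observed 0.82, which may itself contain differences between operations.
- **A reader might infer that the diversion is known before randomisation because it defines eligibility.** Any of the three operations satisfies the criterion, so eligibility alone does not show that the choice is settled when the envelope is opened.
- **A reader might infer that an imbalance would go unseen.** Baseline tables and case report form fields are commonly left to the full protocol or analysis plan, so the article's silence does not show that the operation goes unrecorded.

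What stands against these objections is narrow: the covariate list is explicit, claims completeness and leaves out the operation, and the remedy costs almost nothing.

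**Conclusion.** The point holds as a modest, inexpensive improvement. Three operations are eligible, the single list does not balance them, and the enumerated covariates omit them. The chance of a gap of at least 20 points is about 10–23%, assuming two classes with one at 30–50% of 44 patients. The resulting shift is 0 to about 0.27 day for a 20–27 point gap, assuming a class difference of 0 to 1 day. The upper end of that range would need diversion to explain about a third of the variation seen in the retrospective data, if the mix there was similar.

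The primary test remains valid without any change. What is lost is some precision, and the ability to separate an effect of the fluid from an unlucky split of operations in the trial actually obtained. No size can be put on the acid-base and electrolyte outcomes, because the article gives no figures for them by diversion. Severity lies between optional and weakly recommended.

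**What to change.** 1. In Admission day, record the planned diversion (conduit versus continent reservoir) before the envelope is opened. Use the planned class in the analysis, since the operation performed could differ from it.
2. In Statistics, pre-specify an adjusted analysis of first defecation in days, by a linear or time-to-event model, with randomised group and diversion class. State whether it supports or replaces the *t*-test. Adding diversion only to the existing logistic regression would not protect the primary result: that model has no named outcome, while the primary outcome is in days and its test is unadjusted.
3. Use the same covariate in adjusted analyses of the acid-base and electrolyte outcomes.
4. Do not carry postoperative fluid balance into these models. It arises after randomisation, and the Discussion expects the fluid to act through it.

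Cost: one baseline field, a few extra models, one degree of freedom in each, and under 1 percentage point of power if diversion has no effect. No patients or procedures are added. Stratifying the list by the two classes is optional, and only makes sense if the envelopes are not yet prepared. It would need a second envelope series and could leave incomplete blocks.
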